Thus, supporting women with endometriosis through lifestyle interventions may be crucial for symptom management and improving HRQoL. Therefore, the Pain in Endometriosis And the Relation to Lifestyle (PEARL) study examines the effects of two lifestyle interventions: an AIDI and CBT, on endometriosis-related symptoms and HRQoL. Both interventions are tested separately, as well as in conjunction with one another, to examine whether the combination of these interventions has an enhancing effect. To explore a possible underlying biological mechanism as a contributing factor for symptom improvement, the gut and vaginal microbiome, hair cortisol levels, inflammatory markers and immune cell composition in peripheral blood (PB), and menstrual effluent (ME) are being analysed before and after the interventions. In addition, this study aims to identify differences in these biomarkers between women with and without endometriosis to gain a deeper understanding of the pathogenesis of endometriosis. We assume that this will contribute to new insights in diagnostics and potential new treatment strategies for women with endometriosis.

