### Sample size calculation

The calculation of the required sample size for this RCT was conducted for the primary outcome, average pain intensity measured with a Numerical Rating Scale (NRS). Based on preliminary results of our single-arm explorative feasibility study and the RCT of Field *et al*, where a whole-food diet was implemented that restricts ultra-processed foods for pain management in chronic pain patients,^34^ we assume a pre-post correlation of r = 0.3. Although the single-arm trial found an effect (pre-post) of 1 SD, the expected effect size was set at 0.6 SD (–1.14).

For the CBT no pilot data were available. Therefore, the calculation of the effect size for this intervention was based on an RCT describing the efficacy of CBT in enhancing coping strategies, alleviating depression, stress, pain perception and improving the quality of life for women with endometriosis.^35^ In this study an effect of 0.55 SD was observed. For the current RCT this would translate to a similar effect of CBT as of the AIDI, so −1.14. We assume that the pre-post SD σ and correlation will be the same for all arms.

With 40 participants per arm, the precision for the main effects of AIDI and CBT yields an SD of 0.405, providing power greater than 80% for detecting an effect size of 1.14. However, the interaction effect has an SE of 0.57, ie, with a 95% CI for the estimated difference of ±1.12. This allows to observe an interaction effect in the order of magnitude of AIDI and CBT effects.

Based on our pilot-study we expect a dropout rate of 20–25%. Therefore, ten additional participants will be included in each arm of the RCT, resulting in a target sample size of 50 participants per arm, in total 200 women with endometriosis.

The evaluation of differences between HCs and women with endometriosis will be an explorative part of the study to generate preliminary insights. In the literature a sample size of 30–50 is described as a reasonable minimum sample size.^36^ Considering the potential drop-out and the group size in the other arms of the RCT, the total sample size for this RCT will be 250, of which 200 will be women diagnosed with endometriosis and 50 HC women.

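### The sample size section says the trial can observe an AIDI × CBT interaction as large as the single-intervention effects, but its own standard error gives only about 51% power for that

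*Protocol article*

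**What the plan says.** All the planning figures are in the protocol article under Sample size calculation. The AIDI effect is set at 0.6 SD, equal to 1.14 NRS points, and the CBT effect is taken to be the same ("similar effect of CBT as of the AIDI, so −1.14"). On correlation, "we assume a pre-post correlation of r = 0.3". On common variance, "We assume that the pre-post SD σ and correlation will be the same for all arms".

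For the single-intervention effects the section reads "With 40 participants per arm, the precision for the main effects of AIDI and CBT yields an SD of 0.405", and it claims more than 80% power for 1.14. It then turns, with a contrasting word, to the interaction: "the interaction effect has an SE of 0.57", with a 95% CI of ±1.12. From this it concludes: "This allows to observe an interaction effect in the order of magnitude of AIDI and CBT effects". No power is given for the interaction.

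The Introduction states why the two interventions are also tested together: "to examine whether the combination of these interventions has an enhancing effect". The Statistical analysis section assigns main and interaction effects to a regression on the pre-post change that adjusts for the pre-intervention score, with a significance threshold of 0.05.

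**The concern.** The concluding sentence stands in the sample size justification, directly after a statement of more than 80% power. It reassures the reader that an interaction of about 1.14 is within reach. Its only support is that the CI half-width (1.12) is slightly smaller than the assumed effect (1.14). That comparison says what would happen if the estimate landed exactly on 1.14. It does not say how often a true interaction of 1.14 would be declared significant.

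At stake is what can be concluded about an aim named in the Introduction. If readers believe the design can show an interaction of this size, a non-significant result may be given more weight as evidence against synergy than it can bear.

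**Working it through.** **Inputs** (Sample size calculation unless noted)

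- Effect of each intervention: 1.14 points = 0.6 SD
- Pre-post correlation: 0.3, the same in all arms
- Evaluable per arm: 40 (50 randomised, 20–25% dropout)
- Significance level: 0.05 (Statistical analysis). Two-sided is inferred from 1.96 × 0.57 = 1.12.

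**Step 1: reproduce the plan's figures**

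- SD = 1.14 / 0.6 = 1.90
- Baseline-adjusted residual SD = 1.90 × √(1 − 0.3²) = 1.8125
- SE, one arm versus another = 1.8125 × √(2/40) = 0.405, as stated
- Power for 1.14 at that SE = Φ(1.14/0.405 − 1.96) ≈ 80%, as stated
- SE of the interaction (difference of two differences) = 1.8125 × √(4/40) = 0.573, stated as 0.57
- Half-width = 1.96 × 0.573 = 1.12, as stated

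An unadjusted post-score analysis would give an interaction SE of 0.601 and a change-score analysis 0.711. Only the baseline-adjusted model reproduces 0.57, and that is the model to which the Statistical analysis section assigns the interaction.

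The 0.405 is the SE for comparing two arms. A main effect averaged over the other factor would have SE 1.8125 × √(2/80) = 0.287. This does not affect the interaction figure.

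**Step 2: power for the interaction**

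Power = Φ(δ/SE − 1.96)

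| Evaluable per arm | SE | True interaction δ | Power |
|---|---|---|---|
| 40 | 0.573 | 1.14 | Φ(0.03) ≈ 51% |
| 37.5 (25% dropout from 50) | 0.592 | 1.14 | Φ(−0.03) ≈ 49% |
| 50 (no dropout) | 0.513 | 1.14 | Φ(0.26) ≈ 60% |
| 40 | 0.573 | 0.57 | Φ(−0.97) ≈ 17% |

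With the rounded SE of 0.57 the first row is 51.6%. With the noncentral t distribution it is 50.7%. A one-sided test at 0.05 would give about 64%.

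**Step 3: interaction detectable with 80% power**

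(1.96 + 0.84) × 0.573 ≈ 1.6 points, which is 1.4 times the assumed single-intervention effect.

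**Step 4: combined arm against one single-intervention arm**

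- With 40 per arm: SE 0.405, power for 1.14 about 80%
- With 37.5 per arm: SE = 1.8125 × √(2/37.5) = 0.419, power = Φ(1.14/0.419 − 1.96) ≈ 78%

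If the two effects are purely additive, this contrast equals the full effect of the added intervention, 1.14. It therefore measures added benefit and not departure from additivity.

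**The case against.** The best defence is that the sentence is about precision. Power is claimed only for the single-intervention effects. The wider SE and CI of the interaction are printed immediately before the sentence, and the contrasting word signals that the interaction is less well served. Read literally, an estimate of 1.14 with a half-width of 1.12 does exclude zero. The trial was sized on the single-intervention effects, and the Statistical analysis section speaks of estimating interaction effects.

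Much of this stands: the arithmetic in the section is right, and no power promise for the interaction is broken. What does not stand is the conclusion. In a sample size justification, saying that a design allows an effect of a given size to be observed is a statement about what the trial can be expected to show. The printed figures support that for an interaction of 1.14 only about half the time.

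Four stronger readings are tempting but unsupported:

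- **That the trial's central question is left to chance.** The combination is one stated aim beside testing each intervention separately, and only departure from additivity has the low power. Whether the combination beats a single intervention has about 80% power for a difference of 1.14.
- **That a non-significant interaction is to be expected even under strong synergy.** At 1.14 with 40 per arm the two outcomes are about equally likely.
- **That power is lower still because a repeated measures ANOVA is also planned.** That analysis uses a four-level group factor. The interaction is assigned to the baseline-adjusted regression.
- **That the investigators will read non-significance as no synergy.** Nothing in the article says so.

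**Conclusion.** The concluding sentence on the interaction is wrong as written; the SE of 0.57 and the CI of ±1.12 are not. On the plan's own inputs, power for an interaction of 1.14 is about 51% with 40 evaluable per arm and about 49% at the upper end of the expected dropout. Even with no dropout it is about 60%. It is about 17% for an interaction half that size, and 80% power needs about 1.6 points.

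These figures assume SD 1.90, correlation 0.3, common variance across arms, a two-sided test at 0.05 and the baseline-adjusted regression. The sample size for the single-intervention effects is not called into question.

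**What to change.** Replace the concluding sentence with text such as: *Power for an interaction of 1.14 is about 51%; 80% power needs about 1.6 points. The interaction is reported as an estimate with its 95% CI, and a non-significant result is not taken as absence of synergy.*

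Optionally, prespecify SC + AIDI + CBT versus SC + AIDI and SC + AIDI + CBT versus SC + CBT from the same baseline-adjusted model. Label both as tests of added benefit over a single intervention, not of departure from additivity, and state how multiplicity is handled. The power of about 80% (about 78% at 25% dropout) is at an unadjusted 0.05, so any adjustment would lower it.

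The cost is a change of wording, a less favourable stated figure and, if the option is taken, two contrasts from a model already planned. No participants are added.

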### Study population and recruitment

Women with endometriosis will be recruited from six hospitals in the Netherlands, including Radboud University Medical Centre, Amphia Hospital, Rijnstate Hospital, Jeroen Bosch Hospital, Catharina Hospital and St. Antonius Hospital. In all hospitals, a multidisciplinary centre for the diagnosis and treatment of endometriosis is present. Patients diagnosed with endometriosis will be invited to participate in the RCT by their gynaecologist. Those who are interested will be referred to a researcher to assess eligibility based on inclusion and exclusion criteria. HC women will be recruited at the Radboud University, Radboud University Medical Centre and via social media channels.

Eligible participants are women of at least 17 years old, with a confirmed diagnosis of endometriosis or adenomyosis through ultrasound, MRI or surgery, and experiencing pain symptoms with an NRS score >4 (this inclusion criterion is not attributable for HC women). Furthermore, they are nulligravida, premenopausal, have a body mass index (BMI) between 18 and 30 kg/m², scalp hair longer than 4 cm, commit to not change their use of dietary supplements, and willing to follow an AIDI and CBT. Additionally, eligible participants need to be proficient in Dutch.

Exclusion criteria are smoking, following a vegan diet, use of immunosuppressive or psychotropic medication or recurrent miscarriages (>2), a diagnosis of Crohn’s disease, ulcerative colitis, short bowel syndrome, another chronic inflammatory disease, coeliac disease, an eating disorder or a serious mental illness (DSM-V diagnosis).

Before inclusion, a food frequency questionnaire (FFQ), the ‘Eetscore’-FFQ, and a demographic questionnaire will be administered to potential participants. Those who meet the inclusion criteria will be offered informed consent (online supplemental material 1) by an authorised researcher. An independent researcher can be contacted if participants wish to discuss the study with an expert who is not directly involved in the research project but has knowledge about all aspects of the study. Participants can withdraw consent at any time.

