**Methods and analysis:**

The Pain in Endometriosis And the Relation to Lifestyle (PEARL) study is a five-arm randomised controlled trial with a pre-post factorial design with two factors: an AIDI and CBT. The study population will consist of 250 premenopausal women, of whom 200 are diagnosed with endometriosis and experience pain symptoms and 50 are healthy controls (HC). Women with endometriosis will be recruited from one academic tertiary and five secondary hospitals in the Netherlands. They will be randomised (1:1:1:1) among four intervention groups: standard care (SC) (SC group), SC and an AIDI (SC + AIDI group), SC and CBT (SC + CBT group), and SC, AIDI and CBT (SC + AIDI + CBT group). Women with endometriosis will visit the hospital twice during the intervention period, at the start (T0) and end (T2) of the 13-week intervention period. HC will not undergo any of the interventions and will have one hospital visit (T0). Participants will complete questionnaires regarding pain symptoms, HRQoL, physical activity level, sleep, diet quality, pain cognitions, and stress at T0 and T2. Furthermore, they are instructed to collect menstrual effluent, a vaginal swab and a faecal sample. During the study visits, peripheral blood will be drawn and scalp hair samples will be taken. The primary outcome is average pain, measured using a numerical rating scale. Secondary outcomes focus on HRQoL, inflammation, immune system characteristics, vaginal- and gut microbiome, and hair cortisol levels. These are considered to reflect potentially underlying mechanisms of the effect of both interventions on the primary outcome. Biological samples and questionnaires of women with endometriosis and HC will be compared to establish the differences in secondary outcomes.

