## Methods and analysis

### Study design

This is a study protocol for a randomised controlled trial (RCT) with a pre-post factorial design with two factors: an AIDI and CBT. Women with and without endometriosis will be included, resulting in an RCT with five arms. Women with endometriosis will be randomised among four arms: a control group receiving standard care (SC group) and three intervention groups: receiving standard care and adhering to an AIDI (SC + AIDI group), receiving standard care + CBT (SC + CBT group), and receiving standard care, adhering to an AIDI, and receiving CBT (SC + AIDI + CBT group). The fifth arm is allocated to serve as the healthy control (HC) group (women without endometriosis diagnosis). HCs will not receive any of the interventions. An overview of the study design is presented in figure 1. This protocol was developed in accordance with the Standard Protocol Items: Recommendations for Interventional Trials reporting guidelines.^31^

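### The entry rule admits adenomyosis without endometriosis, but these women are labelled and compared with controls as endometriosis cases, and controls are not required to be free of adenomyosis

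*Protocol article*

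**What the plan says.** All references are to the Protocol article.

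- **Entry rule** (Study population and recruitment): eligible women are those "with a confirmed diagnosis of endometriosis or adenomyosis through ultrasound, MRI or surgery".
- **Invitation route** (same section): "Patients diagnosed with endometriosis will be invited to participate in the RCT by their gynaecologist". Adenomyosis is not mentioned here.
- **Label in the abstract** (Methods and analysis): "200 are diagnosed with endometriosis and experience pain symptoms and 50 are healthy controls (HC".
- **Label in the sample size section**: "of which 200 will be women diagnosed with endometriosis and 50 HC women".
- **Control definition** (Study design): "The fifth arm is allocated to serve as the healthy control (HC) group (women without endometriosis diagnosis". The exclusion list in Study population and recruitment does not name adenomyosis.
- **Use of the groups**: the Introduction aims to find biomarker differences between women with and without endometriosis, with pathogenesis, diagnostics and treatment in view. Statistical analysis compares these two groups at baseline by Welch's ANOVA, or Kruskal-Wallis if the data are not normal. The sample size section calls this part explorative and gives no effect size or power for it.
- **Diagnosis data** (Variables): the method and year of diagnosis and the type of endometriosis are recorded. Adenomyosis status is not listed by name.

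**The concern.** The entry rule and the group label do not describe the same population. The rule is met by endometriosis, by adenomyosis, or by both; the label and the planned comparison speak of endometriosis only. The control definition is the complement of the label, not of the entry rule. A woman with known adenomyosis and no endometriosis therefore meets the diagnostic criterion for a case and is not shut out of the control group by its definition.

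What is at stake is the interpretation of the baseline comparison of immune markers, microbiome and hair cortisol. If the case group is a mixture, its difference from controls estimates a mixture of two disease effects, while the aim names one. The label also matters for the randomised results, which would be reported for women with endometriosis although the entry rule is wider.

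**Working it through.** **Is there a planned figure to reproduce?** Not for this comparison. The stated precision belongs to the randomised pain comparison: SD = 1.14/0.6 = 1.9; baseline-adjusted SD = 1.9 × √(1 − 0.3²) = 1.8125; SE for 40 versus 40 = 1.8125 × √(2/40) = 0.405, as printed. Neither the controls nor the split of cases by diagnosis enters that calculation.

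**What the comparison estimates.** Let ΔE be the true mean difference between endometriosis and disease-free controls on a marker, and ΔA the same for adenomyosis only. Let a be the share of cases with adenomyosis only and b the share of controls with known adenomyosis. Then

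observed difference = (1 − a)ΔE + (a − b)ΔA.

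This equals ΔE for every marker only if a = b = 0. Otherwise it depends on ΔA, which the plan does not separate out. That is the attribution problem, and it does not require the difference to shrink: with ΔE = 0, a > 0 and b = 0, a difference of a × ΔA would still be credited to endometriosis.

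**When does dilution occur?** Write ΔA = (1 − k)ΔE, where k = 1 means adenomyosis-only women resemble controls and k = 0 means they resemble endometriosis cases. Then

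observed difference = ΔE × [1 − ka − (1 − k)b].

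At k = 1 the loss comes only from the case group (a); at k = 0 it comes only from the control group (b). None of a, b and k is in the documents.

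**Illustration with assumed values.** Take b = 0, 200 cases, 50 controls and two-sided alpha 0.05 (the document gives 0.05 without sidedness). With clean groups, a standardised difference of 0.443 has 80% power.

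| a (assumed) | k (assumed) | share of ΔE kept, 1 − ka | observed d | power |
|---|---|---|---|---|
| 0 | any | 1.00 | 0.443 | 80% |
| 10% (20 women) | 0 | 1.00 | 0.443 | 80% |
| 10% (20 women) | 0.5 | 0.95 | 0.421 | 76% |
| 10% (20 women) | 1 | 0.90 | 0.399 | 71% |
| 20% (40 women) | 0 | 1.00 | 0.443 | 80% |
| 20% (40 women) | 0.5 | 0.90 | 0.399 | 71% |
| 20% (40 women) | 1 | 0.80 | 0.354 | 61% |

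**Cost of removing these women from the case group.** With a common SD, the SE is proportional to √(1/n cases + 1/50).

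- 200 cases: √0.02500 = 0.1581.
- 180 cases: √0.02556 = 0.1599, an increase of 1.1%.
- 160 cases: √0.02625 = 0.1620, an increase of 2.5%.

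The 50 controls dominate the variance, so a clean case definition costs little precision.

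**The case against.** The strongest defence is that the overlap is formal. Cases are invited by gynaecologists as endometriosis patients, so adenomyosis-only women may be few or none. Controls are called healthy, come from the university, the medical centre and social media, and may not have another chronic inflammatory disease. The control wording is a short gloss in a condensed article, and the full protocol may contain more. The comparison is declared explorative, and controls play no part in the randomised analysis.

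Much of this stands. It limits the likely number of such women and the weight of the point. It does not remove the contradiction. If only endometriosis patients are meant, the adenomyosis alternative in the entry rule should not be there; if it is meant, the label is wrong. Fuller control criteria elsewhere would not settle the case label.

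A reader might go further and infer that the comparison is diluted from both sides, because the pain criterion is waived for controls ("this inclusion criterion is not attributable for HC women") and undiagnosed endometriosis could enter that group. The documents do not support this. Case-side dilution needs adenomyosis-only women to resemble controls, which is not documented. The Introduction's prevalence of about 10% is for all endometriosis; women with a diagnosis are already excluded from the controls, so it is at most a ceiling for undiagnosed disease. More detailed control criteria may sit in the full protocol. Nor would a pain ceiling for controls be a clear improvement: cases are selected for NRS above 4, so a ceiling at 4 would separate the groups completely on pain, and a marker difference could no longer be told apart from an effect of pain.

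**Conclusion.** The point holds as an inconsistency between the entry rule, the group label and the control definition. Its firm consequence is one of attribution: followed as written, the baseline comparison may estimate a mixture of endometriosis and adenomyosis differences under the name of endometriosis. Dilution is possible but conditional. It depends on the adenomyosis-only share, on any known adenomyosis among controls, and on how far adenomyosis resembles either group on each marker. Since none of these is documented, no single loss figure can be defended; the table only shows how the result moves with the assumptions, including no loss at all. The reach is limited to an explorative comparison and to how the randomised population is described. The randomised comparison is among cases only, and its sample size does not change.

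**What to change.** 1. **Case-control comparison.** Define cases as women with confirmed endometriosis, with or without adenomyosis. Show adenomyosis-only women as a separate group, or run a sensitivity analysis without them.
2. **Controls.** State that they have no known endometriosis and no known adenomyosis.
3. **Data.** Confirm that the diagnosis fields listed under Variables identify adenomyosis-only status. If they do not, add the item while inclusion is running (planned to the end of 2026) and complete it for women already enrolled.
4. **Randomised comparison.** Keep everyone as randomised and describe the population as endometriosis and/or adenomyosis in the abstract, the sample size section and the analysis. Alternatively, reconcile the entry rule with the endometriosis label.

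The cost is a change of wording, an analysis filter and possibly one data item. The downside is a slightly smaller case group in an explorative comparison, with an SE increase of about 1% to 2.5% if 10% to 20% of cases were set aside (assumed shares).
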